#### 2.1.4. Outcomes.

The primary outcome is the time-adjusted and weight-adjusted average or median self-administered dose of propofol in mcg/kg/min.

Secondary outcomes include

Initial enthusiasm at the idea of using a VR headset during surgery assessed by research staff on a 10-point Likert scale for all participants, prior to intervention allocation as part of a questionnaire;Level of anxiety and information requirement measured preoperatively by research staff using the Amsterdam Preoperative Anxiety and Information Scale (APAIS) [18];Incidence of intraoperative and postoperative adverse events such as bradycardia (heart rate < 50 bpm), desaturation (SpO_2_ < 92%) and hypotension (MAP < 60) as well as subjective adverse events, such as cybersickness or nausea documented intraoperatively by the anesthesiologist and research staff based on real-time clinical observation or patient self-reporting;Average or median total time, in minutes, during which the VR headset was worn, as well as the percentage of that time relative to the overall duration of the surgery, recorded by dedicated research staff in the operating room using a time log;Average or median total duration in minutes spent by the patient on the VR scenario chosen, and the order in which VR scenarios were presented, recorded by dedicated research staff in the operating room using a time log and a case report form (CRF);Percentage of patients that switched scenarios;Percentage of patients that removed the headset before the end of the surgery;Percentage of patients requiring additional local anesthesia;Weight-adjusted average or median administration of intraoperative IV fentanyl in mcg/kg;Weight-adjusted average or median administration of intraoperative IV ketamine in mg/kg;PACU length of stay (LOS) measured from PACU admission to PACU discharge, based on the PACU nursing records;Ease of use of the technology and enjoyment of the first scenario chosen assessed post-operatively on a 10-point Likert scale in the intervention group only as part of a postoperative questionnaire administered by dedicated research staff;Overall satisfaction with the experience assessed post-operatively on a 10-point Likert scale in both groups as part of a postoperative questionnaire administered by dedicated research staff.Exploratory outcomesNOL index readings over time per patient, recorded continuously intraoperatively via a finger probe, automatically stored and extractable by dedicated research staff from the PMD-200 monitor with precise timepoints. NOL index spikes will be defined;PCS bolus administration timepoints, automatically recorded by the pump device and extracted by dedicated research staff.

Exploratory analysis will focus on evaluating NOL trends over time and assessing whether NOL peaks are associated with PCS administration timepoints.

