#### 2.1.3. Interventions.

Prior to entering the operating room, all participants will receive an explanation on the use of intraoperative PCS. For those in the intervention group, a short video will introduce all three VR scenarios, after which participants will select their preferred scenario, which will then be documented.

Upon arrival in the operating room, participants will undergo standard monitoring, including non-invasive blood pressure measurement, pulse-oximetry, and continuous electrocardiography using the Dräger Infinity C700 monitor (Dräger Medical, Lübeck, Germany). Throughout the entire duration of surgery, the NOL index finger probe, which is connected to the PMD-200 monitor (Medasense Biometrics Ltd, Ramat Gan, Israel) will be applied. All intraoperative data and events will be recorded on the research computer.

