The attending anesthesiologist will perform PV block before surgery according to their usual practice. Only anesthesiologists with a minimum of 10 PV blocks performed within the last year will be qualified to administer this procedure to trial participants. Standardized doses of intravenous (IV) sedation (0.15 mg/kg of propofol) and IV analgesia (0.5 mcg/kg of fentanyl) will be administered to all participants prior to realization of the PV block and will be repeated if necessary. Once the block is complete, the participant is positioned supine, and the surgeon is ready for disinfection, the VR headset will be applied to those in the intervention group and their chosen scenario will begin. A dedicated research staff member will be present in the operating room throughout the procedure to manage all aspects of the VR intervention, including assisting with headset application, adjusting the VR scenarios upon patient requests, and addressing any technical issues or patient discomfort related to the VR system. Notably, the interactive VR scenarios do not require significant hand or arm movement, as they rely solely on eye-tracking software to aim within the game. The only manual action required is pressing the controller trigger at specific time points. If at any time the patient expresses a desire to discontinue VR during the surgery, we will first offer them an alternate scenario. If they reiterate their willingness to stop, with or without having experienced the new scenario, the headset will be removed for the remainder of the surgery. In case of adverse events attributable to VR gear, such as cybersickness, discontinuation of VR immersion will be at the discretion of the anesthesiologist as well as the patient.

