### 2.2. Assignment of interventions

Electronic randomization of the participants will be performed by an independent third party, using the National Cancer Institute’s Clinical Trial Randomization tool [24]. Specifically, we will randomize participants in a 1:1 ratio using a maximal randomization method, allowing a maximum tolerated imbalance of 3. The randomization sequence will then be implemented in the REDCap application (Vanderbilt University) [25]. Each participant’s allocation will be sealed in an opaque envelope and handed to the dedicated research staff not involved in patient care. The envelope will be opened at the patient’s entry into the operating ward, after confirming that the surgery will be performed under regional anesthesia. The intervention will not be blinded to participants or personnel after allocation.

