### 2.3. Data collection, management and analysis

#### 2.3.1. Data collection methods.

We will collect data at baseline, intraoperatively and postoperatively to assess primary and secondary outcomes. Participant socio-demographic information, medical history and current medication, will be collected from their medical chart. Their education level and familiarity with VR technology will also be recorded through a preoperative questionnaire. Pre-operative anxiety levels will be assessed using the APAIS, a six-item questionnaire designed to measure both anxiety and the desire for information before surgery. The scale provides an overall anxiety score ranging from 4 to 20 and an information-seeking score ranging from 2 to 10, with higher scores indicating greater preoperative anxiety and a stronger desire for information, respectively. A postoperative questionnaire will be used to collect data on patient satisfaction. It is of note that, aside from the APAIS, both our preoperative and postoperative questionnaires are self-composed and have not yet undergone formal scientific validation.

NOL index data from the PMD-200 medical monitor will be automatically collected by the device. Other intraoperative events, such as propofol self-administration, as well as the use of fentanyl or ketamine, will be manually recorded. Postoperative outcomes will be collected through questionnaires administered to participants prior to their discharge from the PACU, at which point we will also record PACU length of stay (LOS). Adverse events of any kind will be documented when spontaneously reported or observed clinically.

We will monitor and document the number of participants who withdraw from the study. If a participant wishes to discontinue their involvement, they will be removed from the study at their request, and no further data will be collected or retained after their withdrawal.

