#### 2.3.2. Data management.

Data from this study will be collected and managed using REDCap electronic data capture tools hosted at Maisonneuve-Rosemont hospital. Research staff will systematically double-check all data entries for completeness and accuracy before final submission. Each participant will be assigned a unique identification number upon enrollment to maintain confidentiality and ensure anonymization.

All collected data will be securely stored on a designated research computer, which will remain offline and be located in a restricted area in Maisonneuve-Rosemont hospital. Notably, this computer will utilize the integrated event-tagging system of the PMD-200 or the BetterCare software (provided by Dräger, Lübeck, Germany), which is connected to the Dräger anesthesia workstation. Usage of this computer will be limited to authorized research personnel, who will need encrypted logins to access study data.

To promote data quality, double data entry will be implemented for our primary outcome. Furthermore, regular, informal audits will be conducted by the research team to verify the accuracy of the study data.

After study completion, electronic data will be retained on secure, encrypted servers for a period of 7 years, as per local institutional and ethical guidelines. Physical copies of patient information, such as consent forms, will be securely stored in a locked file cabinet in the anesthesiology department.

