#### 2.4.2. Potential harms.

The devices used in the study include a VR headset wirelessly paired with a tablet for broadcasting immersive scenarios. These devices do not interfere with intraoperative monitoring, and the risk of adverse events associated with their use is very low.

Any incidence of adverse effects, spontaneously reported or directly observed, will be documented and assessed as part of our secondary outcomes.

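### Bradycardia, desaturation and hypotension have numeric cut-offs but are captured by unblinded observation or report, which leaves this secondary safety comparison open to detection bias of unknown size and direction

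*Protocol article*

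**What the plan says.** Section 2.1.4 lists as a secondary outcome "Incidence of intraoperative and postoperative adverse events such as bradycardia (heart rate < 50 bpm), desaturation" (SpO2 below 92%) and hypotension (MAP below 60), together with subjective events such as cybersickness and nausea. The item ends by saying that events are "documented intraoperatively by the anesthesiologist and research staff based on real-time clinical observation or patient self-reporting".

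Two other sections state how adverse events are captured. Section 2.3.1: "Adverse events of any kind will be documented when spontaneously reported or observed clinically". Section 2.4.2: "Any incidence of adverse effects, spontaneously reported or directly observed, will be documented and assessed as part of our secondary outcomes".

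On who observes, section 2.2 states "The intervention will not be blinded to participants or personnel after allocation", and section 2.1.3 states "A dedicated research staff member will be present in the operating room throughout the procedure to manage all aspects of the VR intervention".

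On recorded data, section 2.1.3 gives all participants non-invasive blood pressure, pulse oximetry and continuous ECG on one named monitor, and adds "All intraoperative data and events will be recorded on the research computer". Section 2.3.2 says that this computer uses "the integrated event-tagging system of the PMD-200 or the BetterCare software"; the software is described as connected to the anesthesia workstation.

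**The concern.** An event defined by a cut-off can be determined from a recorded signal without judgement. The text instead makes its capture depend on someone noticing it or reporting it, and the people in the room know the arm. A brief dip in SpO2 may be logged more readily, or less readily, when a headset is in use and a staff member is occupied with it. Any such difference would appear in the results as a difference between patients.

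The comparison matters because the abstract motivates VR by the risks of IV sedation, hypoxemia among them, and section 1.2 makes the incidence of desaturation, bradycardia and hypotension a secondary objective. The one bias safeguard that section 4.1.1 offers is that patient-controlled sedation limits the anesthesiologist's influence on propofol dosing. That does nothing for event detection. Double data entry (section 2.3.2) covers the primary outcome only.

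**Working it through.** The plan gives no figure on this point to reproduce. The check is a reading of the sections together, followed by an illustration.

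**1. Which capture rule applies to the three events?** Taken alone, the closing clause in section 2.1.4 could attach only to the subjective events that precede it. Section 2.3.1 covers adverse events of any kind, and section 2.4.2 repeats the rule and ties it to the secondary outcomes. So the rule reaches the threshold-defined events. No section says that the cut-offs will be applied to stored vital signs. Elsewhere the same outcome list does name a record where one is meant: the monitor for NOL, the pump for bolus times, and PACU nursing records for length of stay.

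**2. Do the observers know the arm?** Yes, by section 2.2.

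**3. Is another source available?** Section 2.1.3 (same monitoring for everyone, all intraoperative data to the research computer) implies it. Two statements stop short of confirming it. Section 2.3.2 offers the NOL monitor's tagging or the workstation software as alternatives, and only the latter is described as linked to the workstation. Section 2.3.1 names only NOL data as automatic and has other intraoperative events recorded by hand.

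**4. What could unequal detection do?** Inputs from the protocol: 100 participants at 1:1, so 50 per arm, and two-sided alpha 0.05. Assumed, because the documents give no values: the true proportion with an event, the probability that an event is recorded, and no false positives.

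Apparent rate = true rate × detection.
Apparent risk ratio = true risk ratio × (detection VR ÷ detection control).

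No true difference, detection 90% in one arm and 70% in the other:

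| True rate, both arms | Apparent rates | Spurious difference | SE = √[p1(1−p1)/50 + p2(1−p2)/50] | Difference ÷ SE |
|---|---|---|---|---|
| 10% | 9% v 7% | 2 points | 5.4 points | 0.4 |
| 20% | 18% v 14% | 4 points | 7.3 points | 0.5 |
| 30% | 27% v 21% | 6 points | 8.5 points | 0.7 |

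The apparent risk ratio is 0.70 ÷ 0.90 = 0.78 in every row. With 80% or 50% detection in the second arm it is 0.89 or 0.56.

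True difference, 30% control v 15% VR (risk ratio 0.50). Power is by the normal approximation with pooled variance under the null, where p̄ is the mean of the two apparent rates: Φ{[(p1−p2) − 1.96√(2p̄(1−p̄)/50)] ÷ SE}.

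| Detection, control / VR | Apparent rates | Risk ratio | Power |
|---|---|---|---|
| 100% / 100% | 30% v 15% | 0.50 | 43% |
| 70% / 90% | 21% v 13.5% | 0.64 | 17% |
| 90% / 70% | 27% v 10.5% | 0.39 | 56% |
| 50% / 50% | 15% v 7.5% | 0.50 | 22% |

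Rows two and three show that the bias can mask or exaggerate an effect. Row four shows that equal but incomplete detection leaves the risk ratio unchanged and still costs power.

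**The case against.** **The clause concerns subjective events only.** Self-report cannot detect a MAP below 60, so this is a fair reading of section 2.1.4 in isolation. It does not survive sections 2.3.1 and 2.4.2, which cover all adverse events.

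**Reading a monitor against a cut-off is itself clinical observation, and both arms have the same monitoring.** This stands in part. Section 2.1.3 also uses SpO2 below 92% and MAP below 60 within its criteria for conversion to general anesthesia, so the anesthesiologist must watch two of the three limits in both arms. That limits the plausible size of the problem. It does not remove it, because what gets written down still depends on an unblinded person.

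**The illustration is small and assumed.** Correct. At 90% v 70% the spurious differences are below one standard error, and nothing in the documents supports those detection rates or a direction.

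**A condensed article may leave algorithm details elsewhere.** True of artefact rules and coding. But the article does state a capture method, and the point concerns that stated method.

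**Stronger readings to avoid.** A reader might infer that an objective record is already in place and is being ignored. The documents do not establish this: storage of heart rate, SpO2 and MAP is implied, not spelled out, and no section says that stored data will not be used. A reader might also infer that postoperative events have no source, because section 2.1.4 speaks of intraoperative documentation. The general rule in section 2.3.1 is not limited to surgery and so covers them.

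**Conclusion.** The concern holds as a risk to one secondary safety comparison. Three threshold-defined events are captured by report or observation, the observers know the allocation, and no stated safeguard addresses event detection. The size and direction of any bias cannot be derived from the documents. The 2 to 6 point figures rest wholly on assumed event rates and detection probabilities, and show only how the mechanism works. They should not be read as an estimate, nor as evidence that the plan favours VR.

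The primary outcome, self-administered propofol, is unaffected, and no figure in the protocol changes. This is a cheap improvement to a secondary outcome, conditional on confirming what the research computer stores.

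**What to change.** - Confirm that heart rate, SpO2 and MAP are stored automatically for every participant, and state which system stores them. Where a signal is not stored, name the anesthesia record as the source.
- Derive intraoperative bradycardia, desaturation and hypotension from those data, using the cut-offs already in section 2.1.4. Use one prespecified rule with artefact handling, applied identically in both arms by someone without the allocation code.
- Keep observation and self-report for cybersickness, nausea and any other adverse event. The list in section 2.1.4 is not exhaustive, so this route must stay open for objective events beyond the three.
- Optionally, as a clarification only, name the PACU nursing records as the source for postoperative events. Those records are also made by personnel who are not blinded, so this would not remove observer influence there.

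The cost is an extra data export and a short script, with no change to treatment, visits or sample size. Two limits remain. Monitor signals contain artefacts, and non-invasive blood pressure is intermittent, so hypotension counts will depend on the measurement interval. One rule applied to both arms does not make up for readings taken more often in one arm, so the interval should be recorded.

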**Fig 1 pone.0327555.g001:**
[figure not shown]
VR headset and scenario choices. A Paperplane Therapeutics VR headset; B Scenario 1 – Calm; C Scenario 2 – Puzzle; D Scenario 3 – Action.

In both groups, the PCS protocol will consist of 0.15 mg/kg boluses of IV propofol with a lockout period of 2 minutes; additional clinician boluses may be administered based on the lead anesthesiologist’s judgment. For breakthrough pain, local anesthesia can be utilized by the surgical team. The anesthesiologist can also administer 0.5 mcg/kg doses of IV fentanyl and, if insufficient, 0.15 mg/kg doses of IV ketamine. If one of the following criteria are met, the anesthesiologist will switch the participant to general anesthesia: inadequate surgical anesthesia despite attempting all previous measures, persistent hemodynamic or respiratory instability (mean arterial pressure < 60 mmHg despite fluid resuscitation and vasopressors or SpO_2_ < 92% that does not respond to non-invasive oxygenation methods) and any surgical complication requiring general anesthesia.

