#### 2.3.3. Statistical methods.

Descriptive statistics will be used to summarize the data by group. Primary outcome and secondary continuous parameters will be presented as means with standard deviations, or medians with interquartile ranges if the data is skewed or non-normally distributed. Categorical variables will be reported as frequencies (%). 95% confidence intervals (CIs) for proportions or mean/median differences will be presented based on the type of endpoint analyzed, and statistical significance will be determined using an alpha level of 0.05. Parametric, two-sample t-tests will be performed for normally distributed outcomes. Otherwise, a non-parametric Wilcoxon test will be performed.

Univariate analyses will be performed to explore relationships between the primary outcome (total propofol consumption) and other potential variables. Variables showing significant associations (P < 0.05) or clinical relevance will be considered for inclusion in a multivariable linear regression model. To evaluate the fit of our linear regression models, we will examine R^2^ and adjusted R^2^ values to assess explanatory power. In addition, residual plots and diagnostic statistics will be used to evaluate assumptions of linearity, normality, and homoscedasticity. If model fit is inadequate, appropriate transformations or alternative modeling strategies will be considered. Logistic regression may be employed where appropriate for binary secondary or exploratory outcomes. To evaluate the fit of our logistic regression models, we will conduct the Hosmer-Lemeshow goodness-of-fit test; P > 0.05 will be considered indicative of an adequate model fit. If poor fit is detected, alternative modeling strategies, such as transformations or interaction terms, will be considered.

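### If fewer than half of each arm receives ketamine, the rule for skewed data reports a median difference of 0, so this secondary outcome should also give the percentage treated

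*Protocol article*

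**What the plan says.** Section 2.1.4 (Outcomes) lists as a secondary outcome "Weight-adjusted average or median administration of intraoperative IV ketamine in mg/kg". It defines no count or percentage of ketamine users. The neighbouring rescue outcome is handled differently: "Percentage of patients requiring additional local anesthesia".

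Section 2.1.3 (Interventions, the text after Fig 1) sets out when the drug is given. It states "For breakthrough pain, local anesthesia can be utilized by the surgical team", and then "The anesthesiologist can also administer 0.5 mcg/kg doses of IV fentanyl and, if insufficient, 0.15 mg/kg doses of IV ketamine".

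Section 2.3.3 (Statistical methods) decides how a dose is summarised and compared. Continuous outcomes are shown as means with standard deviations, "or medians with interquartile ranges if the data is skewed or non-normally distributed". Normally distributed outcomes are compared by t-test. "Otherwise, a non-parametric Wilcoxon test will be performed". For the effect estimate, "95% confidence intervals (CIs) for proportions or mean/median differences will be presented based on the type of endpoint analyzed".

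No section gives an expected rate of ketamine use.

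**The concern.** A drug held back until fentanyl has proved insufficient will probably be given to a minority of patients. Its dose then has a large spike at exactly zero and a short right tail. That is skewed, so the rule in section 2.3.3 leads to the median and, for the effect, to a median difference. The median of a variable that is zero in more than half of patients is zero, whatever happens in the rest. The plan can therefore print the same estimate, 0, when use is equal in the two arms and when it has doubled or tripled in one of them.

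Section 1.2 lists the quantity of ketamine administered as a secondary objective. The trial is open-label and the anesthesiologist gives the drug at discretion, so a reader of the results will want to know whether its use differed between arms. An estimated difference of 0 could be taken as an answer to that when it is not one.

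**Working it through.** **Inputs.** The plan states no figure for ketamine, so there is none to reproduce. Arm size comes from sections 2.1.6 and 2.2: 100 participants randomised 1:1 gives 50 per arm (45 per arm if 90 are evaluable). The dose unit, 0.15 mg/kg, is from section 2.1.3. All rates of use below are assumptions.

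**When the median is 0.** With 50 patients the median is the mean of the 25th and 26th ordered values. It is 0 if at most 24 patients received ketamine. With 45 patients the limit is 22.

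**Baseline below which a change is invisible.** Both arms must stay under one half.
- Doubling: 2p < 0.5, so p < 25%.
- Tripling: 3p < 0.5, so p < 16.7%, about 17%.

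These limits apply to the observed proportions. Close to the limit, sampling variation can carry an arm past one half, as the next step shows.

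**Probability that one arm's median is 0.** This is P(X ≤ 24) with X binomial(50, p), or P(X ≤ 22) with n = 45.

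| True use | n = 50 | n = 45 |
|---|---|---|
| 5% to 20% | >0.999 | >0.999 |
| 30% | 0.998 | 0.998 |
| 40% | 0.902 | 0.914 |
| 45% | 0.716 | 0.751 |
| 50% | 0.444 | 0.500 |
| 60% | 0.057 | 0.087 |

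**Both medians 0.** The arms are independent, so the probabilities multiply. With 50 per arm:
- 10% vs 20%: above 0.99
- 10% vs 30%: about 0.998
- 20% vs 40%: about 0.90
- 15% vs 45%: about 0.72
- 20% vs 60%: about 0.06

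**Worked example.** Take 5/50 users in one arm and 15/50 in the other, each given one dose of 0.15 mg/kg.
- Medians: 0 and 0, difference 0.
- Hodges-Lehmann shift (median of all 50 × 50 = 2,500 pairwise differences): 35 × 45 + 15 × 5 = 1,650 differences are 0, 15 × 45 = 675 are +0.15 and 35 × 5 = 175 are −0.15. The median is 0.
- Interval for that shift by the usual large-sample ranks: 1,250 ± 1.96 × √(2,500 × 101/12) = 1,250 ± 284, i.e. ranks 966 to 1,534. Ranks 176 to 1,825 are all 0, so the interval is 0 to 0.
- Means: 5 × 0.15/50 = 0.015 and 15 × 0.15/50 = 0.045 mg/kg, difference 0.030 mg/kg.
- Wilcoxon test: p = 0.013.
- Risk difference: 30% − 10% = 20 percentage points. Standard error √(0.1 × 0.9/50 + 0.3 × 0.7/50) = 0.0775; Wald 95% CI 20 ± 15.2, about 5 to 35 points.

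**Does the planned test lose sensitivity?** Simulated Wilcoxon power (50 per arm, 2,000 runs, 1 + Poisson(0.5) doses per user assumed) against the calculated power of a two-proportion test:

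| Use | Wilcoxon | Proportions |
|---|---|---|
| 5% vs 15% | 0.37 | 0.38 |
| 10% vs 20% | 0.28 | 0.29 |
| 10% vs 30% | 0.71 | 0.71 |

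The two are practically the same.

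**Does the interquartile range help?** With 50 per arm the upper quartile is also 0 with probability 0.999 at 10% use, 0.81 at 20% and 0.22 at 30%. It becomes informative only once use passes about 25%.

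**The case against.** The strongest reply is that the planned analysis would still find a difference. This is right. A reader might infer that the plan cannot show any between-arm difference in ketamine use; the documents do not support that, because section 2.3.3 provides a Wilcoxon test, which responds to the proportion of users with about the power of a test of proportions. What remains is that the p-value would have no usable estimate beside it.

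Second, low use is an inference. Only the step from fentanyl to ketamine is an explicit sequence in section 2.1.3. Section 2.3.3 screens out only grossly ineffective blocks, while section 2.2 has the envelope opened on entry to the operating ward without mentioning block success. If ketamine use reached 60% in one arm, that arm's median would rarely be 0. The point must therefore stay conditional.

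Third, section 2.1.4 permits an average as well as a median, and section 2.3.3 allows intervals for proportions. That leaves room for a sensible analyst, but the stated rule for skewed data still points a mostly-zero dose to the median, and no proportion is defined for ketamine.

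Fourth, tabulation detail often sits in a statistical analysis plan that is not shown. Here, however, the article itself fixes both the outcome measure and the summary rule.

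Finally, it is tempting to extend the point to fentanyl. Section 2.1.3 gives every participant fentanyl before the block, and section 2.1.4 does not say that this dose is excluded from the intraoperative total. If it counts, no fentanyl median is 0. The same problem would arise only if post-block doses alone were counted and fewer than half of each arm needed them.

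**Conclusion.** The point holds in a conditional and limited form. Provided fewer than half of each arm receives ketamine, which is likely but undocumented, the rule in section 2.3.3 returns medians of 0 and 0 and a median difference of 0, even with a doubling from below about 25% or a tripling from below about 17%. The defect is confined to the effect estimate and its interval for one secondary outcome: a significant p-value could stand beside an estimated difference of 0.

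A reader might also infer that such a result would wrongly show that ketamine did not replace propofol. The article does not assign the outcome that role; it only asks how much was given. The primary outcome and its conclusion are unaffected. This is a minor improvement.

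**What to change.** In sections 2.1.4 and 2.3.3, report for each arm the number and percentage of patients receiving any intraoperative ketamine, with a risk difference and 95% CI. This brings ketamine into line with additional local anesthesia, which is already defined as a percentage of patients. Give the mean dose in mg/kg per arm as the accompanying quantity instead of relying on the median.

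The cost is a sentence or so in each section. Section 2.3.1 already provides for recording ketamine use, so no data collection, dose or clinical rule changes.
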